**Table 6-4 RAD001 dose levels for dose adjustment**

| Dose level                 | Dose and schedule    |
|----------------------------|----------------------|
| Starting Dose              | 10 mg daily          |
| -1 (-50% of starting dose) | 5 mg daily           |
| -2 (-50% of dose level -1) | 5 mg every other day |

If a patient has already decreased 2 dose levels, no further dose reduction is permitted. Patients requiring a further dose reduction from 5 mg every other day will be required to discontinue study treatment.

### **6.7.3 Other concomitant medications**

Patients must be instructed not to take any additional medications (over-the-counter, herbal or other products) during the study without prior consultation with the investigator. All medications taken within 30 days of starting study treatment should be reported on the Concomitant Medications/Significant Non-drug Therapies CRF. **Enzyme-inducing antiepileptic drugs are allowed on this study.**

**The following guidelines must be adhered to during the study:**

Investigational or commercial anti-proliferative agents other than study drug (including other mTOR inhibitors, e.g., sirolimus, temsirolimus) are prohibited.

### **Inhibitors of CYP3A4 and/or PgP**

- Co-administration with strong inhibitors of CYP3A4 (e.g., ketoconazole, itraconazole, ritonavir) or P-glycoprotein (PgP) should be avoided.
- Co-administration with moderate CYP3A4 inhibitors (e.g., erythromycin, fluconazole) or PgP inhibitors should be used with caution. If patient requires co-administration of moderate CYP3A4 inhibitors or PgP inhibitors, reduce the dose of everolimus to half the currently used dose. Additional dose reductions to every other day may be required to manage toxicities. If the inhibitor is discontinued the everolimus dose should be returned to the dose used prior to initiation of the moderate CYP3A4/PgP inhibitor.
- Seville orange, star fruit, grapefruit and their juices affect P450 and PgP activity. Concomitant use should be avoided.

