|                                                               | 
therapy. If no safety concerns are seen within the next 7 days, the dose can be increased again one additional increment up to a maximum of twice the daily dose used prior to initiation of the strong CYP3A4 inducer.
 
 
This dose adjustment of everolimus is intended to achieve similar AUC to the range observed without inducers. However, there are no clinical data with this dose adjustment in patients receiving strong CYP3A4 inducers. If the strong inducer is discontinued the everolimus dose should be returned to the dose used prior to initiation of the strong CYP3A4/PgP inducer.
 
 
A list of medications with known effects on CYP3A and PgP are included in Table 6-5. RAD001 may affect the response to vaccinations making the response to the vaccination less effective. Live vaccines and close contact with those who have received live vaccines should be avoided while a patient is treated with RAD001. Otherwise, the use of other concomitant medication/therapy deemed necessary for the care of the patient is allowed. The investigator should instruct the patient to notify the study site about any new medications he/she takes after the start of the study drug. All medications (other than study drug) and significant non-drug therapies (including physical therapy and blood transfusions) administered after the patient starts trial therapy must be listed on the Concomitant Medications/Significant Non-drug Therapies CRF.
 |

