RAD001 is mainly metabolized by CYP3A4 in the liver and to some extent in the intestinal wall. RAD001 is also a substrate of P-glycoprotein (PgP). Therefore, absorption and subsequent elimination of systematically absorbed RAD001 may be influenced by medicinal products that interact with CYP3A4 and/or P-glycoprotein. *In vitro* studies showed that RAD001 is a competitive inhibitor of CYP3A4 and of CYP2D6 substrates, potentially increasing the concentrations of medicinal products eliminated by these enzymes. In two phase III clinical trials in patients following kidney transplantation, strong inhibitors of CYP3A4 (azoles, antifungals, cyclosporine, erythromycin) have been shown to reduce the clearance of RAD001 therapy thereby increasing RAD001 blood levels. Conversely, Rifampin, a strong inducer of CYP3A4, increases the clearance of RAD001 thereby reducing RAD001 blood levels. Caution should be exercised when co-administering RAD001 with CYP3A4 inhibitors or inducers.

Pharmacokinetic drug to drug interactions with cancer agents have been evaluated in phase Ib studies. Based on currently available results, gemcitabine ([Study 2101] part 2) and paclitaxel ([Study 2104]) did not alter RAD001 pharmacokinetics to a clinically relevant extent whereas imatinib notably increased RAD001 exposure with a mean increase in AUC by a multiple of 3.7 for RAD001 administered weekly and two-fold for RAD001 administered daily [Study 2206]. Exposure to RAD001 in the presence of letrozole did not exceed that in monotherapy [Study 2108]. Co-administration of RAD001 did not influence pharmacokinetics of gemcitabine, imatinib or letrozole. Exposure to paclitaxel in the presence of RAD001 was slightly decreased (average by 23%). RAD001 pharmacokinetics in transplant patients was investigated in special populations such as subjects with hepatic or renal impairment, various ethnic groups and pediatric renal transplant patients. In subjects with mild-moderate hepatic impairment, mean AUC of RAD001 is increased by 2-fold while renal impairment does not affect the pharmacokinetics of RAD001. Age, weight (both over the adult range) and gender do not affect the pharmacokinetics of RAD001 to any clinically relevant extent. Also, pharmacokinetics does not alter in Asian patients whereas black patients have a 21% higher clearance compared to non-blacks. A single, escalating-dose study in Japanese subjects did not show a significant difference in dose-normalized systemic exposure.

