**Table 6-5 Clinically relevant drug interaction: inducers and inhibitors of isoenzyme CYP3A**

| INDUCERS                                                                                                                                                                                                                                                                                                                                                                                                                                                                                                                                                                                                                                               |
|--------------------------------------------------------------------------------------------------------------------------------------------------------------------------------------------------------------------------------------------------------------------------------------------------------------------------------------------------------------------------------------------------------------------------------------------------------------------------------------------------------------------------------------------------------------------------------------------------------------------------------------------------------|
| 
Strong inducers:
avasimibe, carbamazepine, mitotane, phenobarbital, phenytoin, rifabutin, rifampin (rifampicin), St. John's wort (hypericum perforatum)
 
Moderate inducers:
bosentan, efavirenz, etravirine, genistein, modafinil, nafcillin, ritonavir, [talviraline], thioridazine, tipranavir
                                                                                                                                                                                                                                                                                                                    |

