| rifampin, St John's wort                                                                                                                                                                                                                                                                                                                                                                                                                                                                                                                                     |
| PgP INHIBITORS and PgP/CYP3A DUAL INHIBITORS                                                                                                                                                                                                                                                                                                                                                                                                                                                                                                                 |
| amiodarone, azithromycin, captopril, carvedilol, clarithromycin, conivaptan, diltiazem, dronedarone, elacridar, erythromycin, felodipine, fexofenadine, fluvoxamine, ginkgo (ginkgo biloba), indinavir, itraconazole, lopinavir, mibefradil, milk thistle (silybum marianum), nelfinavir, nifedipine, nitrendipine, paroxetine, quercetin, quinidine, ranolazine, rifampin, ritonavir, saquinavir, Schisandra chinensis, St John's wort (hypericum perforatum), talinolol, Telaprevir, telmisartan, ticagrelor, tipranavir, tolvaptan, valsopodar, verapamil |
| Reference: Internal Clinical Pharmacology Drug-drug interaction (DDI) memo, updated Oct. 2, 2011, which summarizes DDI data from three sources including the FDA's "Guidance for Industry, Drug Interaction Studies", the University of Washington's Drug Interaction Database, and Indiana University School of Medicine's Drug Interaction Table.                                                                                                                                                                                                          |

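### Read literally, section 6.7.3 with Table 6-6 halves everolimus for rifampin and St John's wort, which the same section names as strong CYP3A4 inducers calling for a considered dose increase

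*Protocol*

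**What the plan says.** **The halving rule.** Section 6.7.3, under inhibitors of CYP3A4 and/or PgP, states: "If patient requires co-administration of moderate CYP3A4 inhibitors or PgP inhibitors, reduce the dose of everolimus to half the currently used dose". The synopsis repeats the rule. Neither place names a PgP inhibitor.

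**The only PgP list.** Table 6-6 has a row headed "PgP INHIBITORS and PgP/CYP3A DUAL INHIBITORS". It contains "quinidine, ranolazine, rifampin, ritonavir, saquinavir, Schisandra chinensis" and, continuing, "Schisandra chinensis, St John's wort (hypericum perforatum), talinolol". The inducer row of the same table consists of rifampin and St John's wort alone.

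**The inducer rule.** Sections 6.7.2 and 6.7.3 and the synopsis say to avoid strong CYP3A4 inducers and, if one is required, to consider raising everolimus in 5 mg steps to at most twice the current dose. Rifampin and St John's wort are both named there. Table 6-5 lists as strong inducers "avasimibe, carbamazepine, mitotane, phenobarbital, phenytoin, rifabutin, rifampin (rifampicin" and also St John's wort. Section 1.4.4 states: "Rifampin, a strong inducer of CYP3A4, increases the clearance of RAD001 thereby reducing RAD001 blood levels".

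**The cross-references.** The synopsis says "A list of medications with known effects on CYP3A and PgP are included in" Table 6-5, but that table is titled "Clinically relevant drug interaction: inducers and inhibitors of isoenzyme CYP3A". No dosing text cites Table 6-6.

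**EIAEDs.** The synopsis excepts them from the interaction guidelines. Section 6.7.3 says they are allowed, but its lead-in to the guidelines contains no exception. Section 6.7.2 has neither statement.

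**The concern.** A site treating a patient who needs rifampin can find that drug under two headings with opposite dose instructions. By the protocol's own pharmacology, rifampin already reduces exposure, so halving the dose would reduce it further. The halving is worded as an instruction, whereas the increase is first something to consider. Section 6.7.3 says its guidelines must be followed, and section 12 allows no authorized deviations. A site looking for the rule that prevails will not find one.

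The EIAED mismatch raises a related question: does the increase apply to a patient already taking phenytoin, carbamazepine or phenobarbital at randomization? The synopsis exception suggests not, though the synopsis's own inducer rule names these three drugs. Sections 6.7.2 and 6.7.3 name them without an exception. The protocol also says there are no clinical data with this dose adjustment in patients on strong inducers, so sites should not have to guess when it applies.

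**Working it through.** There is no plan figure to reproduce. The check sets the rules side by side and works out the doses they imply.

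**Step 1: which rules reach the two drugs**

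| Place | Rifampin | St John's wort | Dose consequence |
|---|---|---|---|
| 6.7.3 halving rule | not named | not named | halve for any required PgP inhibitor |
| Table 6-6, inhibitor row | listed | listed | none stated in the table |
| Table 6-6, inducer row | listed | listed | none stated in the table |
| 6.7.2 and 6.7.3 inducer rule | named | named | avoid; if required, consider an increase |
| Table 6-5, strong inducers | listed | listed | none stated in the table |
| 1.4.4 | lowers RAD001 levels | not mentioned | none stated |

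The halving reaches the two drugs only by joining the class rule to Table 6-6. The inducer rule reaches them by name. No sentence ranks the two.

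**Step 2: the doses, from the 10 mg/day start (section 4.2)**

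- Halving rule: 10 × 0.5 = 5 mg/day.
- Inducer rule, first step, 7 days after the inducer starts: 10 + 5 = 15 mg/day.
- Inducer rule, second step, after a further 7 days without safety concerns: 15 + 5 = 20 mg/day, which equals the cap of 2 × 10 = 20 mg/day.
- Widest gap: 20 / 5 = fourfold, in opposite directions.

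The increase as a whole is to be considered. Within it, the first increment is worded as something that should be done and the second as something that can be done.

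**Step 3: how many patients use an EIAED at baseline**

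Inputs: 66 patients on RAD001, and the stratum ratios named in section 10.7. Stratum 1 is TSC with EIAED use.

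| Ratio (strata 1:2:3) | Share in stratum 1 | Expected of 66 |
|---|---|---|
| 3:6:1 | 3/10 | 19.8, about 20 |
| 3:3:2 (planned) | 3/8 | 24.75, about 25 |
| 4.5:4.5:1 | 4.5/10 | 29.7, about 30 |

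These counts exclude placebo patients who later take open-label RAD001. They are expected numbers of baseline users, not of misdosed patients. The inducer rule names three of the seven EIAEDs listed in section 6.5, but that section calls all seven strong CYP3A4 inducers, so the three names do not clearly limit its reach.

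**Step 4: what the text implies for baseline EIAED users**

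The increase is timed from the start of the inducer and capped by the dose in use before it was initiated. Every patient starts at 10 mg/day, section 4.2 describes dose changes only as reduction, interruption or return to the starting dose, and Table 6-4 has no level above 10 mg. All of this points to an increase only for inducers started on study, but it is not stated.

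**The case against.** The strongest reply is that the reader has to assemble the halving. No dosing text cites Table 6-6, and the table carries no dose instruction. It is an interaction reference that also lists substrates, and its inhibitor row includes drugs such as itraconazole and ritonavir that section 6.7.3 says to avoid rather than halve for. The inducer rule names both drugs, the table that section 6.7.3 does cite classes both as strong inducers, and such drugs are to be avoided in the first place. On EIAEDs, section 6.7.3 states the permission in bold immediately before the guidelines, and the timing wording does not fit a drug already taken at randomization.

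Most of this stands. It makes actual misdosing unlikely and largely settles the intent on EIAEDs. It does not remove the literal conflict: Table 6-6 is the only place a site can learn what counts as a PgP inhibitor, and nothing exempts the two drugs once it gets there.

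Three stronger readings are tempting and unsupported:

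- A reader might infer that Table 6-6 misclassifies the two drugs. The protocol lists them on purpose or not as both PgP inducers and PgP inhibitors, and nothing in it shows that either entry is wrong. The fault lies in the dosing rule.
- A reader might infer that the 20 to 30 baseline EIAED users are at risk of misdosing, or that about 25 is a ceiling. The documents give no count of misdosed patients, and a ratio the protocol itself considers gives about 30.
- A reader might infer that EIAEDs are permitted only by the synopsis. Section 6.7.3 permits them too; only the exception from the guidelines is confined to the synopsis.

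**Conclusion.** The main point holds as a conflict of wording. For rifampin and St John's wort, two rules within section 6.7.3 lead from 10 mg/day to 5 mg/day or to as much as 20 mg/day. The first is the wrong direction for rifampin by section 1.4.4 and, for both drugs, by their classification as strong inducers. Confidence in the textual overlap is high. The practical risk is low, because the drug-specific rule would usually be followed.

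The EIAED point is a secondary clarification: a real mismatch between the synopsis and the body, largely answered by the timing wording and the uniform starting dose. How many patients either point would affect is unknown. The figure of about 20 to 30 of 66 rests on the stratum ratios named in section 10.7 and describes baseline EIAED use only.

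Severity is minor. Randomization, power and the primary analysis are unaffected.

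**What to change.** 1. In section 6.7.3 and the synopsis, add that drugs named as strong CYP3A4 inducers, including rifampin and St John's wort, follow the inducer rule only and are exempt from halving for PgP inhibitors.
2. In both places, cite Table 6-6 as the PgP list, correcting the synopsis pointer to Table 6-5. Leave the classification in Table 6-6 as it is.
3. Carry the synopsis's EIAED exception into sections 6.7.2 and 6.7.3, and state that the increase applies to strong inducers started on study. A patient on a stable EIAED at randomization then stays at 10 mg/day, with safety reductions as usual.

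The cost is a few sentences and one corrected cross-reference, at the next amendment or by letter to sites. The stratification list, sample size and analysis stay as they are.

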### **Inducers of CYP3A4 and/or PgP**

- Avoid the use of strong CYP3A4 inducers. If patient requires co-administration of strong CYP3A4 inducers (i.e., phenytoin, carbamazepine, rifampin, rifabutin, phenobarbital, St. John's wort), an increase in the dose of everolimus up to twice the currently used daily dose should be considered, 5mg increments. Enzyme induction usually occurs within 7-10 days, therefore everolimus dose should be increased by one increment 7 days after the start of the inducer therapy. If no safety concerns are seen within the next 7 days, the dose can be increased again one additional increment up to a maximum of twice the daily dose used prior to initiation of the strong CYP3A4 inducer.
- This dose adjustment of everolimus is intended to achieve similar AUC to the range observed without inducers. However, there are no clinical data with this dose adjustment in patients receiving strong CYP3A4 inducers. If the strong inducer is discontinued the everolimus dose should be returned to the dose used prior to initiation of the strong CYP3A4/PgP inducer.

Table 6-5 lists clinically relevant CYP3A inhibitors inducers and the definition of strong and moderate inhibitors/inducers.

RAD001 may affect a patient's response to vaccinations making the response less effective. Live vaccines and close contact with those who have received live vaccines should be avoided while a patient is treated with RAD001.

Otherwise, the use of other concomitant medication/therapy deemed necessary for the care of the patient is allowed. The investigator should instruct the patient to notify the study site about any new medications he/she takes after the start of the study drug. All medications (other than study drug) and significant non-drug therapies (including physical therapy and blood transfusions) administered after the patient starts study drug and for up to 8 weeks (56 days) after study drug discontinuation must be listed on the Concomitant Medications/Significant Non-drug Therapies CRF.

**Table 6-5 Clinically relevant drug interaction: inducers and inhibitors of isoenzyme CYP3A**

| INDUCERS                                                                                                                                                                                                                                                                                                                                                                                                                                                                                                                                                                                                                                               |
|--------------------------------------------------------------------------------------------------------------------------------------------------------------------------------------------------------------------------------------------------------------------------------------------------------------------------------------------------------------------------------------------------------------------------------------------------------------------------------------------------------------------------------------------------------------------------------------------------------------------------------------------------------|
| 
Strong inducers:
avasimibe, carbamazepine, mitotane, phenobarbital, phenytoin, rifabutin, rifampin (rifampicin), St. John's wort (hypericum perforatum)
 
Moderate inducers:
bosentan, efavirenz, etravirine, genistein, modafinil, nafcillin, ritonavir, [talviraline], thioridazine, tipranavir
                                                                                                                                                                                                                                                                                                                    |
| INHIBITORS                                                                                                                                                                                                                                                                                                                                                                                                                                                                                                                                                                                                                                             |
| 
Strong inhibitors:
boceprevir, clarithromycin, cobicistat, conivaptan, elvitegravir, indinavir, itraconazole, ketoconazole, lopinavir, mibefradil, nefazodone, nelfinavir, posaconazole (Krishna et al 2009), ritonavir, saquinavir, telaprevir, telithromycin, tipranavir, troleandomycin, voriconazole
 
Moderate inhibitors:
Amprenavir, aprepitant, atazanavir, casopitant, cimetidine, ciprofloxacin, cyclosporine, darunavir, diltiazem, dronedarone, erythromycin, fluconazole, fosamprenavir, grapefruit juice (citrus paradisi fruit juice), imatinib, schisandra sphenanthera, tofisopam, verapamil
 |

